### 4.2 Population

This study will include adult HIV-1 infected patients who are about to initiate or have already initiated first-line ART. Patient enrolment and randomisation will be performed at two different time points. Timing and criteria for enrolment and randomisation are as follows:

1. ART naïve patients: Patients are eligible for enrolment at initiation of treatment with first-line ART. Randomization is performed after availability of the first routine VL measurement, performed at month 6 of treatment.
2. Patients on ART: Patients are eligible for enrolment after  $\geq 1$  year of virologically suppressive first-line ART and only if a last VL with a result of  $<1000$  copies/mL was performed within the last 6 months. Randomisation is performed 6 months after the last VL result.

A total number of 600 patients will be randomized into two trial arms. The trial will be conducted on-site at one of the clinical facilities of Ndlovu Care Group (<http://www.ndlovucaregroup.co.za/>), one of the partners in the project. This facility, Ndlovu Medical Centre, is situated in the town of Elandsdoorn, Limpopo, South Africa, and provides medical service to local South African patients who are unable to pay medical insurance. The

---

\* In this protocol timing of study visits and procedures is indicated in months (defined as a period of 28 days) after the date on which ART was initiated. For the purpose of this protocol, whenever an event is timed at a certain month, a margin of 28 days before and 28 days after the exact date must be maintained. Hence, if a patient has been on ART since September 4th, 2014, his/her month 6 study follow-up visit is due Thursday, February 19th 2015, and will fall within the time frame of Thursday, January 22nd 2015 and Thursday, March 19th 2015.

Ndlovu Care Group distributes antiretroviral medication in the framework of the South African Department of Health HAART programme. This clinic is currently providing ART to >3600 patients. Patients on ART return to the clinic monthly for collection of medication, pill count and adherence counselling, which allows intensification of monitoring without substantial change of the infrastructure or frequency of visits.

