#### 5.2.7 Questionnaires

Questionnaires will be used to measure a variety of parameters relevant to the trial study objectives (see table 2). For data on adherence (e.g. number and reasons of missed doses, reasons and motives for non-adherence), drug toxicity and physical and mental wellbeing, a questionnaire developed by the AIDS Clinical Trial Group (ACTG) will be used. This validated self-report questionnaire has been included in several clinical trials and consists of a baseline and follow-up questionnaire. A modification of the ACTG baseline questionnaire will be used at enrolment, and a shortened version of the ACTG follow-up questionnaires will be used at month 3, 6, 9, 12, 15, 18, 21 and 24 (study end) in both study arms. Data on adherence from the standard pill count form that is applied at each drug pick-up visit (monthly or every 2 months) will also be collected.

Data relevant to the study objectives regarding social and psychological risk factors are partly covered by the ACTG questionnaires. A newly designed questionnaire will be used that will incorporate the sections from the ACTG questionnaires (mental and physical health), NIDS (socioeconomic status and family structure), CHAMP (substance abuse and sexual risk behavior). This questionnaire will contain item scales modified from the ACTG original, matched to local socio-economic and cultural context, as well as record several additional parameters such as stigmatization (Kalichman & Simbayi) and coping abilities (CISS). Data on Quality of life (QoL) of study participants will be used for evaluation of the cost-effectiveness of the trial intervention and will be recorded using the WHO QOL HIV (BREF) questionnaire and EQ5D questionnaire.

In a substudy participants who become lost to follow-up during the trial and who are successfully traced >28 days after a missed clinical visit (as per standard-of-care clinical procedures) are approached for informed consent to perform an additional questionnaire interview during a home visit.

Questions will be bundled in a comprehensive baseline and study end questionnaire (baseline and month 24), and a brief follow-up questionnaire which will be recorded per 3-monthly study visit (month 3, 6, 9, 12, 15, 18 and 21). In lost to follow-up patients who enter the substudy questionnaires will be recorded during a home visit. For a full overview of parameters and questionnaires, see table 2.

Table 2: overview of questionnaire data

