#### 5.3.1.7 Tracing 28 days after a missed visit

As per clinical standard-of-care, patients who do not return to the clinic within 28 days after a missed scheduled appointment will receive a phone call and questionnaire on current location and contact details and treatment status is administered. If telephonic contact cannot be made a home visit is performed when the patient has consented to this. During home visits the standard of care questionnaire on current location and contact details and treatment status is administered.

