#### 5.3.1.8 Immediate tracing after a missed visit

In addition to standard-of-care and if informed consent is given, tracing procedures in study participants are expanded by performing home visits in all participants regardless of successful telephonic tracing, during which an in-depth questionnaire interview on reasons for LTFU and a finger prick for sampling of a DBS is performed.

As per standard-of-care, 90 days after a missed scheduled appointment retention status will be re-evaluated. Patients not returned to the clinic will be contacted telephonically and per home visit in case of no telephonic contact to confirm their current treatment status. At this time point the definite patient study outcome will be recorded.

If not retrieved, a patient will be reported as lost to follow up and excluded if two subsequent study visits are missed and the retention procedure for both visits is unsuccessful. If ART is stopped or interrupted, patients will also be excluded from the study. Study exclusion will in no way compromise access to medical care.

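### Section 5.3.1.8 closes follow-up by two unreconciled rules, and the 90-day rule can record a definite outcome while a valid month-24 viral load can still be taken

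*Protocol*

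**What the plan says.** Protocol section 5.3.1.8 contains two rules in consecutive paragraphs.

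- **90-day rule.** "90 days after a missed scheduled appointment retention status will be re-evaluated". Patients who have not returned are contacted to confirm their treatment status, and "At this time point the definite patient study outcome will be recorded". One missed appointment is enough to start this clock.
- **Two-visit rule.** A patient who is not retrieved is reported as lost and "excluded if two subsequent study visits are missed and the retention procedure for both visits is unsuccessful".

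The timing footnote to sections 4.1 and 4.2 defines a month as 28 days and says that "a margin of 28 days before and 28 days after the exact date must be maintained".

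Two other places use 28 days. Section 5.3.1.7 starts a phone call or home visit for "patients who do not return to the clinic within 28 days after a missed scheduled appointment". Section 5.2.7 describes a substudy of "participants who become lost to follow-up during the trial and who are successfully traced >28 days after a missed clinical visit".

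Section 6.7.3 sizes one of its three outcomes on viral load above 1000 copies/ml at month 24: 15% control, 5% intervention, 10% loss a year, 216 patients per arm. Section 4.1 randomises 600 patients and follows them for 18 months after randomisation.

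**The concern.** The 90-day rule speaks of a definite outcome after one missed appointment. The two-visit rule keeps the patient in the trial until a second visit has also been missed. The protocol does not say which one ends follow-up, whether a visit counts as missed on the appointment date or when its window closes, or whether a patient who reappears after either step still gives a month-24 sample.

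Patients who miss visits are plausibly those off drug and viraemic, so a month-24 viral load not drawn in them is unlikely to be missing at random. The trial is open-label, so whoever decides whether a returning patient is still in the study may know the arm. An analysis plan cannot repair this later, because it cannot recover a sample that was never taken.

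**Working it through.** **Inputs.** Month of 28 days and window of ±28 days (footnote to sections 4.1 and 4.2); the 90-day and two-visit rules (5.3.1.8); immediate tracing that ends about 1–2 weeks after the missed visit (5.3.1.6); 15% v 5%, 10% loss a year and 216 per arm (6.7.3); 300 per arm (5.1.2, 5.1.3); 18 months of follow-up (4.1). Section 6.7.3 gives no alpha or power for the month-24 outcome. Two-sided 0.05 and 90% are assumed.

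**The plan's own figures.**

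- Footnote example: start on 4 September 2014 plus 6 × 28 = 168 days gives 19 February 2015, with a window from 22 January to 19 March. This matches.
- Sample size: (1.960 + 1.282)² × (0.15×0.85 + 0.05×0.95) / 0.10² = 183.9, so 184 evaluable per arm. Loss over 18 months is 1.5 × 10% = 15%, and 184 / 0.85 = 216.5. This agrees with the stated 216.

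**Calendar.** Month 21 is day 21 × 28 = 588 (window 560–616). Month 24 is day 24 × 28 = 672 (window 644–700).

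| Event | Day reached | Month-24 window left |
|---|---|---|
| Month 21 missed on due date, +90 | 588 + 90 = 678 | 700 − 678 = 22 days |
| Month 21 missed at earliest appointment, +90 | 560 + 90 = 650 | 50 days |
| Month 21 missed at an appointment on day 610, +90 | 700 | 0 days |
| Month 24 missed on due date, +90 | 672 + 90 = 762 | closed 62 days before |
| Month 24 missed at earliest appointment, +90 | 644 + 90 = 734 | closed 34 days before |

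The overlap therefore arises from a missed month-21 visit with an appointment before day 610. A missed month-24 visit produces none.

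**Two-visit rule.** Take a patient who misses months 18 and 21. Retention for month 21 has failed by about day 588 + 14 = 602 if it means the 1–2 week procedure, or by day 678 if it includes the 90-day step. Both fall before day 700. A patient excluded then who returns inside the month-24 window is already out of the study, and the protocol provides no month-24 viral load for them.

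**Size of the month-21 overlap.** Loss of 15% spread evenly over six visits (assumed) is 0.15 / 6 × 300 = 7.5 patients per arm first missing month 21. The base is 300 × 0.85 = 255 evaluable per arm, with 38.25 and 12.75 expected events.

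- Half return and half of those are viraemic (assumed): 3.75 more measured and 1.875 more events per arm. Control (38.25 + 1.875) / 258.75 = 15.5%; intervention (12.75 + 1.875) / 258.75 = 5.7%. The difference is 9.9 points and power is 96%, against 97% at 15% v 5% with 255 per arm.
- All 7.5 measured and viraemic (extreme): 45.75 / 262.5 = 17.4% and 20.25 / 262.5 = 7.7%. Power is 92%.

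**The case against.** The strongest reply is that section 5.3.1.8 is a ladder of tracing steps with a single exclusion rule at the end. Only the two-visit sentence uses the words lost and excluded, and it applies only to patients not retrieved. Section 5.3.1.6 counsels retrieved patients to come in for a study visit. Day 90 is also 6 days after the next visit falls due, so the second visit is normally overdue by then. Much of this stands: reading the definite outcome as final loss is a natural inference for an untraced patient, but it is not stated. The reply does not say what a definite outcome means for someone who returns on, say, day 685, or what happens to a patient already excluded.

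A reader might infer four stronger claims that the documents do not support:

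- **28 days as a third definition of loss.** Section 5.3.1.7 uses it to trigger tracing and assigns no status. Section 5.2.7 uses it to describe who is approached for a substudy. For an appointment on the due date it also coincides with the end of the visit window.
- **A window conflict for patients who miss only month 24.** Their 90-day point comes after the window has closed. They can never meet the two-visit rule, but they are not excluded either; the value is simply missing.
- **A threat to the stated power.** With 300 randomised per arm against 216 required, there is none of note.
- **A demonstrated difference between arms.** Section 5.3.1.6 applies the same initial tracing in both. Open-label conduct leaves room for different decisions but does not show them.

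It is also fair to say that section 5.3.1.8 separately excludes patients whose ART is stopped or interrupted. Reconciling the two loss rules alone leaves that sentence in place. How missing month-24 values are analysed may properly be left to a statistical analysis plan; whether the sample is drawn may not.

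**Conclusion.** The point holds in a limited form. Section 5.3.1.8 has two end-of-follow-up rules that are not reconciled. Under the protocol's own calendar, the 90-day rule can record a definite outcome 22 days before the month-24 window closes, or up to 50 days before if the month-21 appointment was early. Patients excluded under the two-visit rule who come back have no month-24 sample provided for.

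The overlap touches about 7.5 patients per arm, and on the middle assumption the month-24 rates move by well under one percentage point in each arm. These sizes rest on even loss over six visits and on assumed return and viraemia shares; the calendar result needs none of these. The overlap assumes that the 90 days run from the appointment date, as the text says. What is at stake is avoidable and probably informative missing data after randomisation. It is worth correcting because the correction is cheap.

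**What to change.** Reconcile the two rules in section 5.3.1.8 so that final status is set only after the relevant visit window has closed, and say whether a visit is missed at the appointment date or at window close.

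Then add the sentence that matters most: a recorded outcome or loss status does not end endpoint collection. Any randomised, consenting patient who is at the clinic within the month-24 window has the month-24 viral load taken, and it is analysed in the assigned arm. Unifying the wording without this sentence would only be a clarification. The sentence should also be read against the exclusion for stopped or interrupted ART in the same section, so that the two do not contradict each other.

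The cost is a short protocol clarification, a few extra viral load tests in patients already at the clinic, and slightly later closure of final status for some patients.

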## 1 SUMMARY

|                         |                                                                                                                                                                                                                                                                                                                                                                                                                                                                                                                                                                                                                                                                                                                                                                     |
|-------------------------|---------------------------------------------------------------------------------------------------------------------------------------------------------------------------------------------------------------------------------------------------------------------------------------------------------------------------------------------------------------------------------------------------------------------------------------------------------------------------------------------------------------------------------------------------------------------------------------------------------------------------------------------------------------------------------------------------------------------------------------------------------------------|
| Rationale        | We propose a novel low-cost intensified HIV-1 treatment monitoring strategy that will allow for (1) detection of therapy failure at an early stage, (2) immediate identification of patients with major non-adherence to therapy enabling intensified and tailored adherence counselling, (3) early detection of drug resistance prior to accumulation of resistance mutations, and (4) avoiding treatment switches to second-line regimens when drug resistance is absent. As this strategy is expected to reduce the duration of viremia during therapy failure it is expected to contribute to lower rates of transmission of (drug-resistant) HIV.                                                                                                              |

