## 3 OBJECTIVES

### 3.1 Primary objective – Virological effects of intensified monitoring

To assess the effect of the intensified monitoring strategy versus standard of care monitoring on (1) development and accumulation of resistance mutations and consequential loss of therapeutic options, (2) prevention of unnecessary treatment switches and (3) resuppression rates after intensified counselling.

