### 5.1.3 Intervention arm follow-up – Intensified HIV treatment monitoring

300 patients randomly assigned to this arm will be monitored using the investigational intensified monitoring strategy. This strategy consists of 3-monthly VL monitoring at month 9, 12, 15, 18, 21 and 24 (after start of ART in initiating patients or after the last VL measurement in patients on ART). If a VL measurement > 1000 copies/mL is detected, the patient will be called back for a follow-up study visit at the next monthly medication collection visit (4 weeks after detection of elevated VL). Upon arrival DLM is performed, the VL measurement is repeated, and a DBS prepared and stored at room temperature. Procedures following this depend on the result of DLM:

- If drug levels are detected by DLM, the result of the VL measurement is awaited. If the repeat VL is >1000 copies/ml, the DBS is shipped directly by courier to the WHO reference laboratory for drug resistance testing. The reference laboratory will provide feedback by means of a digital resistance report to the coordinating research physician. The patient will be called back for a second follow-up study visit at the next monthly medication visit (8 weeks after detection of elevated VL), either for prescription of second-line therapy or continuation of first-line therapy, guided by the

result of resistance testing.

- If DLM at the first follow-up visit indicates that drug levels are not detected, intensified counselling is performed at the same visit and first-line therapy will be maintained, regardless of the result of the repeat VL measurement. The patient will not be called back and the next VL will be performed at the next scheduled three-monthly time point. However, if the VL result at this visit is again >1000 copies/ml, drug resistance testing will be performed regardless of the outcome of DLM.

For a full overview of study visits and clinical algorithms in the control arm, see Figure 1: ITREMA study flowchart.

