#### 5.2.5 Drug Level Monitoring (DLM)

DLM will be performed in case of a VL >1000 copies/ml at any of the intervention arm study follow-up visits. DLM will take place at a call back visit one month after the visit in which elevated VL was detected, using EDTA-derived plasma obtained at the call back visit. DLM will be performed on-site using a qualitative assay that can be implemented in basic clinical laboratories, and will detect plasma levels of the NNRTI's efavirenz and nevirapine. Results will be reported as either “detectable drug level” or “no detectable drug level”, the latter indicating at least several days of non-adherence over the last week. This result will be reported back to the treating research clinician at the call back visit, who will inform the patient of the result during this visit.

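### Randomised patients whose ART is stopped or interrupted are excluded from the study, which ends outcome collection in the non-adherent failures the strategy targets; the rule is undefined and unreconciled with sections 5.1.1, 5.1.3, 5.2.4.1 and 5.2.5

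*Protocol*

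**What the plan says.** Section 5.3.1.8 of the protocol, on tracing after missed visits, contains two exclusion rules. The first is ordinary loss to follow-up: a patient is "excluded if two subsequent study visits are missed and the retention procedure for both visits is unsuccessful". The second is additional and has no link to attendance: "If ART is stopped or interrupted, patients will also be excluded from the study". It gives no duration, no source of evidence and no restriction to the period before randomisation. Continuous ART before randomisation is already required separately in section 4.5.

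Other sections bear on this:

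- **Aims.** The summary describes the strategy as allowing "immediate identification of patients with major non-adherence to therapy enabling intensified and tailored adherence counselling". The primary objective in section 3.1 includes "3) resuppression rates after intensified counselling". Section 6.1 lists failure without resistance and averted unnecessary switches among the virological outcomes.
- **Drug level monitoring (DLM).** Section 5.2.5 says: "DLM will be performed in case of a VL >1000 copies/ml at any of the intervention arm study follow-up visits". A result of no detectable level is described as "the latter indicating at least several days of non-adherence over the last week".
- **Action on that result.** Section 5.1.3 prescribes counselling at the same visit, and "first-line therapy will be maintained, regardless of the result of the repeat VL measurement". The next VL follows at the next three-monthly visit. Section 5.2.4.1 agrees.
- **Other changes of treatment.** Under section 5.1.1, patients in either arm who switch to second-line therapy stay in three-monthly follow-up.
- **Contact after leaving.** Section 5.5 provides for it only when a participant decides to leave, and only for morbidity and mortality data.

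**The concern.** Interrupting ART is an event after randomisation that lies on the path between a monitoring and adherence strategy and its outcomes. It should be followed and counted. Here it ends participation. Section 5.3.1.2 uses the same term for patients who fail the randomisation criteria and are handed back to clinical care, so the plain meaning is that study visits and sampling stop.

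Three things are at stake. First, month-24 VL and later plasma and dried blood spot (DBS) samples are lost in a group rich in outcome events. This is a rule on data collection, so an analysis population set elsewhere can keep the patient in the denominator but cannot supply the missing result. Second, because an interruption is undefined, a patient with several days without drug could be retained under section 5.1.3 or excluded under section 5.3.1.8. Staff in an open-label trial would decide case by case. Third, drug levels and the more frequent VL tests exist only in the intervention arm, so the chance of documenting an interruption may differ between arms.

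**Working it through.** **Inputs.** Section 6.7.3 gives VL >1000 copies/ml at month 24 as 15% in control and 5% in intervention, loss to follow-up of 10% a year, and 216 patients per arm. Sections 5.1.2 and 5.1.3 give 300 per arm. Section 4.1 gives 18 months of follow-up after randomisation, so loss is 1.5 × 10% = 15%. Significance level and power are not stated for this outcome; two-sided 5% and 90% are assumed. The share of viraemic patients excluded for interruption, *f*, is not in the protocol and is varied.

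**1. The plan's own figure.** With unpooled variance:

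n = (1.960 + 1.282)² × (0.15 × 0.85 + 0.05 × 0.95) / 0.10² = 183.9

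183.9 / 0.85 = 216.3, which matches the stated 216. So 184 evaluable per arm is the planned minimum, and the full 300 per arm gives 300 × 0.85 = 255. Power by the two-proportion normal approximation (pooled variance under the null) is 89.5% at 184 and 96.6% at 255.

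**2. Equal exclusion in both arms.** If a share *f* of patients who would be viraemic at month 24 is removed and nobody else is, the observed rate is p(1 − f)/(1 − pf). For f = 0.30:

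- control: 0.15 × 0.70 / (1 − 0.045) = 0.105 / 0.955 = 11.0%
- intervention: 0.05 × 0.70 / (1 − 0.015) = 0.035 / 0.985 = 3.6%
- difference: 7.4 points instead of 10.0

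| f in both arms | Difference (points) | Power, 184 per arm | Power, 255 per arm |
|---|---|---|---|
| 0 | 10.0 | 89.5% | 96.6% |
| 10% | 9.2 | 86.4% | 95.0% |
| 20% | 8.3 | 82.5% | 92.7% |
| 30% | 7.4 | 77.6% | 89.3% |
| 50% | 5.5 | 64.0% | 77.9% |

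The relative risk hardly moves (0.110 / 0.0355 = 3.1, against 0.15 / 0.05 = 3.0). With equal exclusion the damage is to the risk difference and to power.

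**3. Unequal exclusion with no true effect.** Take 15% in both arms and 255 evaluable per arm, with 10% of viraemic patients excluded in control and 30% in intervention:

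- control: 0.135 / 0.985 = 13.7%, with 255 × 0.985 = 251.2 patients
- intervention: 0.105 / 0.955 = 11.0%, with 255 × 0.955 = 243.5 patients
- spurious difference: 2.7 points; standard error √(0.137 × 0.863 / 251.2 + 0.110 × 0.890 / 243.5) = 0.0295; ratio 0.92
- chance of a significant result: about 15% instead of 5%

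A 10% v 20% imbalance gives 1.3 points and about 7%; 10% v 50% gives 5.6 points and about 51%. Reversing 10% and 30% gives the mirror image, 2.7 points against the intervention.

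**4. Direction by outcome.** The summary counts resistance mutations per patient with therapy failure. Section 2.2 expects a lower risk of resistance in major non-adherence. Removing non-adherent viraemic patients from one arm would lower that arm's month-24 viraemia but raise its mutations per failure. In the intervention arm it would also lower the count of averted switches, which section 6.1 defines as two successive elevated VLs without resistance mutations.

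**The case against.** The strongest objection concerns the tempting further reading: that the rule removes patients more readily in the arm that measures drug levels, and so favours the intervention. The documents do not support this. Sections 5.1.3, 5.2.4.1 and 5.3.1.5 counsel patients with an undetectable level and keep them in follow-up; none makes that result a ground for exclusion. The exclusion sentence stands in the missed-visit section, just after treatment status is confirmed at 90 days, so it reads most naturally as applying to a traced defaulter found off ART. The main routes to discovering an interruption are common to both arms: monthly pick-up with pill counts (section 4.2), adherence questionnaires (5.2.7) and tracing (5.3.1.6 to 5.3.1.8). Control patients with an elevated VL are also called back (5.3.1.4). A calculation with 20% to 50% of viraemic patients excluded in intervention and none in control would give false-positive rates of about 14% to 67%, but the zero in control is an assumption with no basis in the text.

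This objection stands against any claim of established imbalance or known direction. It does not remove the possibility of imbalance: the intervention arm has DLM and six scheduled VLs after randomisation against two, and the trial is open label.

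Other fair points also stand. Who is analysed, and how missing VLs are handled, may be left to an analysis plan. The two-missed-visits rule is ordinary loss to follow-up, already allowed for at 10% a year. Nothing says that data already collected are discarded, and with consent a DBS is taken at a tracing visit. But that single sample does not replace continued sampling and a month-24 VL.

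**Conclusion.** The concern holds in this form: the protocol ends outcome collection, after randomisation, in patients whose ART is stopped or interrupted. It leaves interruption undefined and does not reconcile the rule with the sections that retain patients after several days without drug or after a switch. The group lost belongs to the primary objective, and the lost samples cannot be recovered at analysis.

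No size can be derived from the protocol, because it gives no interruption rate. As illustrations only, equal exclusion of 30% of viraemic patients cuts the planned 10-point difference to about 7.4 points and power from about 90% to about 78% at 184 evaluable per arm. An imbalance of 10% v 30% under no true effect gives about 15% false-positive results at 255 per arm. Both assume that only patients who would be viraemic at month 24 are removed, and both use the two-sided 5% level assumed above. The stated sample size of 216 per arm is not itself in error.

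**What to change.** Reconcile section 5.3.1.8 with sections 5.1.1, 5.1.3, 5.2.4.1 and 5.2.5. For randomised patients, delete exclusion from the study on the ground of ART interruption. State that they remain in outcome follow-up in the arm assigned, by study visit or home tracing, with stored samples and a month-24 VL. Define interruption for data recording and record it as an outcome in the same way in both arms. This changes what is collected, not how patients are treated; the clinical algorithms need no change for this purpose.

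The cost is a short amendment and some extra follow-up contacts. These are not free: study visits are timed to drug pick-up and are not reimbursed (sections 5.3.1.3 and 7.4), and a patient off ART may have no pick-up visit. The tracing, home-visit and DBS procedures already in section 5.3.1 can carry part of the work. The planned sample size is unchanged.
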